#### Study Part 1: effectiveness and durability of effects of orthopedic rehabilitation programs

1.1.1

The primary objective of Study Part 1 is to evaluate the effectiveness of rehabilitation programs for patients with orthopedic impairments. The focus extends beyond the immediate outcomes, aiming to investigate the durability of effects. The criteria for evaluating the effectiveness and durability are: (i) subjective physical and mental health, (ii) work ability, (iii) body weight, and (iv) physical activity. Subjective health and work ability are crucial indicators to return to work which is the main aim of rehabilitation providers. Close correlates of these indicators and a healthy lifestyle are participants' body weight and the amount of regular physical activity in everyday life.

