#### Sampling and participants

2.1.1

Eligibility criteria for participating in the study are that patients need to be at least 18 years old, have basic knowledge of the German language, and the reason for their rehabilitation is an orthopedic impairment prescribed by the German pension fund. There are no further inclusion criteria regarding the type of orthopedic impairment. Participants will be recruited at two different measurement occasions, one before the rehabilitation program starts and one during the first few days of the rehabilitation program. For the first measurement occasion, patients receive information about the study and the first questionnaire via post several weeks before the rehabilitation program starts (t_0_). Rehabilitation centers send out the study material together with the usual information material regarding the rehabilitation program itself. Patients that did not participate in the study at the first measurement occasion can still be recruited at the second measurement occasion (t_1_) which is taking place at the beginning of the rehabilitation program in the rehabilitation centers. Participants that already participated in the first measurement occasion (before rehabilitation started) also fill out the second questionnaire at the beginning of the rehabilitation program (t_1_). This procedure allows for a comparison of the indicators' development from the time without a rehabilitation program with the indicators' development after the rehabilitation program has started. Participants will be informed of the purpose of the study and will give their written consent to participate voluntarily. Currently, five rehabilitation centers in Germany are part of the study. The patients will receive a 50€ voucher, if they fill out the questionnaires at all measurement occasions. Participants are reminded by the research team via e-Mail or phone to fill out the questionnaires to increase participation in the study.

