#### Rehabilitation programs

2.1.2

Orthopedic rehabilitations programs in Germany are offered stationary or as an outpatient program in rehabilitation centers. Typically, rehabilitation programs last three to four weeks and comprise different services such as physiotherapy, medical training therapy, and health education. For some indications, standards for treatments exist based on scientific evidence such as for knee and hip joints, but this is not the case for all orthopedic indications (22). Therefore, the content and structure of rehabilitation programs can vary between rehabilitation centers. Rehabilitation programs at the participating rehabilitation centers will be executed as usual and the impact of the study will be limited to the data collection. Therefore, this treatment is not an intervention provided by the research team, but rather treatment as usual.

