#### Data collection

2.1.3

Data collection started in September 2023 and baseline measurements will be completed approximately in January 2025. The study design consists of nine measurement occasions for participants that are recruited in the time before the rehabilitation program starts (t_0_–t_8_). For participants that are recruited at the beginning of the rehabilitation program in the rehabilitation center, the study comprises eight measurement occasions (t_1_–t_8_). Pre (t_1_) and post (t_2_) measurements are conducted at the beginning and at the end of the rehabilitation program to assess the effectivity. Based on their preference, the participants are contacted by e-mail or mail for the further measurement occasions (t_2_–t_8_). The interval between the measurement occasions after the rehabilitation is completed (t_2_–t_8_) is six months, resulting in a total follow-up period of three years. The study design for Study Part 1 is provided in Figure 1.

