**Figure 1 F1:**
[figure not shown]
Study design of Study Part 1.

Demographic information, including age, gender, nationality, and current employment situation, are asked at enrolment. The participants are also asked to provide contact details for follow-up measurement occasions. Post measurement (t_2_) comprises also information about the rehabilitation program and health indicators for subgroup-analyses. Information regarding the employment status and disability pension are reported to the research team of the Karlsruhe Institute of Technology (KIT) via the Deutsche Rentenversicherung (DRV) Knappschaft-Bahn-See during the last year of follow-up, if participants gave their consent at t_0_ or t_1_. All other instruments described below are used at the baseline measurement (t_0_), the pre and post measurements (t_1_, t_2_), and the follow-up measurements (t_3_–t_8_).

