#### Data analysis

2.1.4

Data will be analyzed by the KIT research team. Questionnaire data are pseudonymized through personal codes and contact details are stored separately from questionnaire data. The identification of participants is possible only through a password-protected, locally stored file by the research team. A research assistant independently checks the accuracy of the data entry. Missing data will be analyzed to what extent they are systematic and, if necessary, treated with multiple imputation or the full-information maximum likelihood approach.

In order to ensure comprehensive analysis and interpretation of the data collected in our study, a multi-faceted statistical approach will be employed. Initially, repeated measures analyses of variance will be utilized to assess changes in subjective health, work ability, BMI, and physical activity behavior over time. This method is particularly effective for analyzing data where multiple measurements are recorded for the same subjects. Analysis of variance with repeated measurement allows for the evaluation of both within-subjects effects (changes over time) and between-subjects effects (differences among groups). In addition, latent growth curve modeling (LGCM) will be implemented to explore the trajectories of the aforementioned parameters across the study period. LGCM provides a flexible framework to model nonlinear growth trajectories, accommodating various shapes of developmental change (35). This is particularly pertinent for our study, as it enables the examination of individual differences in change patterns, thereby offering a deeper understanding of how rehabilitation programs impact individuals over time. Age, gender, the duration and the completement of the rehabilitation program will be included as control variables.

### Methods of Study Part 2

2.2

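### Completion of rehabilitation, and duration if it means actual stay, are post-start variables used as controls in the Part 1 effectiveness models, so the reported time effect can depend on coding

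*Protocol article*

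**What the plan says.** Section 1.1.1 of the protocol article sets the aim: "The primary objective of Study Part 1 is to evaluate the effectiveness of rehabilitation programs for patients with orthopedic impairments". Section 2.1.3 ties effectiveness to the step from t1 to t2, whose "measurements are conducted at the beginning and at the end of the rehabilitation program to assess the effectivity". Section 2.1.1 adds a period before treatment, t0 to t1, as the reference: "This procedure allows for a comparison of the indicators' development from the time without a rehabilitation program".

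Section 2.1.4 names two model families for this. First, "repeated measures analyses of variance will be utilized to assess changes in subjective health, work ability, BMI, and physical activity behavior over time". Second, "latent growth curve modeling (LGCM) will be implemented to explore the trajectories of the aforementioned parameters across the study period". The paragraph ends with the covariates: "Age, gender, the duration and the completement of the rehabilitation program will be included as control variables".

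Section 2.1.3 also says that the t2 questionnaire "comprises also information about the rehabilitation program and health indicators for subgroup-analyses". The article gives no reason for controlling for completion and describes no analysis of all starters without it.

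**The concern.** Age and gender are fixed before treatment; completion is not. It becomes known only after t1, it describes how much of the program was received, and a patient who is doing badly may be less likely to finish. Placing it beside age and gender treats a possible consequence of the patient's course as if it were a baseline characteristic.

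There is also nothing for it to correct. Part 1 compares each patient with himself or herself over time, so completion status does not confound the average change. It can only change the group, or the weighted mix of groups, to which the reported change refers. The t0–t1 reference period has the same problem, because it would be conditioned on an event that lies in its future.

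At stake is the meaning of the primary result. The planning effect is only 0.10 SD, so a modest link between completion and change is enough to move the reported time effect noticeably, or to reverse its sign under some codings.

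**Working it through.** **1. The plan's own figures.** Section 2.1.1 gives a standardized effect of 0.10, f = 0.05, α = 0.05, power 0.80, r = 0.50, eight occasions, a within-between interaction and n = 360. The number of groups is not stated; two are assumed.

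- λ = f²·N·m/(1 − r) = 0.0025 × 360 × 8 / 0.50 = 14.4
- df1 = 7 and df2 = 358 × 7 = 2,506
- power = 0.8003, so 360 is reproduced
- 360/0.85⁷ = 1,123, about 2% from the stated 1,101

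The calculation contains no covariates, so nothing below changes the sample size.

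**2. Set-up of the illustration.** Inputs from the article: mean t1–t2 change μ = 0.10 SD; and r = 0.50, which gives SD of change √(2 × (1 − 0.50)) = 1. Assumed, because the article gives neither: completion proportion p (80% to 95%), and correlation ρ (0 to 0.5) between a patient's underlying tendency to complete and that patient's change.

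**3. Formulas.** Let Δ be the difference in mean change between completers and non-completers. When completion is allowed to act on change, the time effect is:

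- at the completer level: μ + (1 − p)Δ
- at the non-completer level: μ − pΔ
- as the equally weighted mean of both levels: μ + (0.5 − p)Δ
- with completion centred at its sample mean: μ

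Under a normal model the completer mean is μ + ρφ/p and the non-completer mean is μ − ρφ/(1 − p), where φ is the standard normal density at the cut-point.

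**4. Numbers for p = 0.90, ρ = 0.2.** Here φ = 0.1755, so ρφ = 0.0351.

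| Time effect read at | Closed form | Simulation (400,000 patients) |
|---|---|---|
| Completers | 0.10 + 0.0351/0.90 = 0.139 | 0.141 |
| Non-completers | 0.10 − 0.0351/0.10 = −0.251 | −0.255 |
| Equally weighted mean | (0.139 − 0.251)/2 = −0.056 | −0.057 |
| Completion mean-centred | 0.90 × 0.139 + 0.10 × (−0.251) = 0.100 | 0.101 |

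**5. Range over p = 80–95% and ρ = 0–0.5 (simulation).**

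- Completer level: 0.10 to 0.28
- Non-completer level: 0.10 down to −0.93
- Equally weighted mean: 0.10 down to −0.39
- Mean-centred: 0.10 throughout

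At ρ = 0 every coding returns 0.10 apart from simulation error.

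**6. When the sign changes.** With p = 0.90 the equally weighted mean reaches zero at 0.10 − 0.40Δ = 0, that is Δ = 0.25 SD.

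**The case against.** The strongest reply is that adjustment is not restriction. Non-completers stay in the model, and with completion mean-centred the time effect equals that of all starters. This stands. A reader might infer that the reported effect will apply to completers only; the article does not support that, because it does not say at which level of completion the effect will be read.

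A condensed article may also leave coding and centring to the analysis plan. That stands too: missing coding is not the fault raised here. A reader might go further and quote the time effect at zero days of stay, not completed. Such a figure presupposes uncentred covariates, which the article does not state, and uncentred age, a legitimate baseline covariate, would cause the same trouble. In addition, a covariate entered only as a main effect leaves the time contrast unchanged in balanced data, and the average slope of a growth model can be recovered whatever the origin of the covariates.

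Duration is less clear-cut. The article does not say whether planned or actual duration is meant, and planned duration would be fixed before the start. There is also a design reason to consider it: t2 falls at the end of the program and "Typically, rehabilitation programs last three to four weeks", so the t1–t2 interval varies. The point is therefore firmest for completion.

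A reader might also infer that patients without t2 data drop out of the models because program information is collected then. That does not follow. Section 2.1.4 provides for multiple imputation or full-information maximum likelihood if needed, and the article does not say that completion or duration comes only from the t2 questionnaire.

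Finally, there are no randomized arms, so no between-arm comparison is biased. What remains is that the article fixes a post-start covariate for its effectiveness models and sets no all-starters result beside it.

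**Conclusion.** The point holds in a limited form. The choice of completion as a control variable is stated in the article, not left open, and it does not suit an objective about the effectiveness of programs for patients who enter them. It can distort the reported time effect; whether it does depends on the link between completion and change, on whether the covariate acts on the time effect, and on coding.

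In the example the planned 0.10 SD could be reported as anything from about 0.14 to −0.26. These sizes rest on an assumed completion rate and an assumed correlation; they are illustrations, not predictions. For duration the point applies only if actual length of stay is meant. By its position the covariate sentence might refer to the growth curve models alone, but those too are effectiveness models, so the conclusion is the same.

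**What to change.** State that the main Part 1 result is change over time in all patients who start rehabilitation, adjusted only for variables fixed before t1: mean-centred age, gender and, if wanted, planned duration. Say whether duration means planned or actual. Move completion and actual duration to separate analyses labelled as associational or as sensitivity analyses. Make the change before the outcome models are run.

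The cost is a sentence or two in section 2.1.4 and one additional analysis. Data collection and the sample size (360 analysed, 1,101 recruited) stay as they are.

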#### Sampling and participants

2.2.1

Participants of Study Part 1 are eligible for Study Part 2, if they plan to implement an aftercare health behavior on a regular basis after their rehabilitation program ends (e.g., participation in an after-care program). The data collection for this study part has not started yet. Researchers will contact participants that gave their written consent to participate in Study Part 2 at t_0_ or t_1_. Participants will inform the researchers about their planned aftercare health behavior (i.e., the specific days during the week and the time planned to execute the behavior). In the quantitative part of Study Part 2, psychological determinants of the aftercare health behavior will be assessed using Ambulatory Assessment. Researchers will send short questionnaires via the application movisensXS to the participants on different measurement occasions during the week dependent on the selected days and times of the aftercare health behavior. Participants will also be asked whether they performed the planned behavior and to state the reasons if not. Missing planned physical activity sessions are not a reason for dropout, as long as the participant will plan to continue with the health behavior. In the qualitative part of Study Part 2, participants of the quantitative part will be interviewed, which either successfully implemented the aftercare health behavior or failed to implement it on a regular basis. Both groups will be interviewed to gather more information about the reasons that contributed to their success or failure.

As no treatment is planned for Study Part 2, a small effect size is assumed. For sample size estimation with G*Power, the more conservative repeated measures ANOVA is used, because power analysis for multilevel models requires assumptions about several population parameters that were not found in the literature. Estimating the effect size with Cohen's *f* = 0.10, *α* = 0.05, 1-*β* = 0.80, a correlation between the repeated measures of *r* = 0.50 and 12 repeated measures in a repeated measures ANOVA (interaction of within-subject and between-subject effects) resulted in a total sample size of 72 participants. Assuming that 10% of participants drop out of the study each week over a 12-week study period (36), 226 subjects need to be recruited. A purposive sampling (37) will be used to interview (A) people who have integrated the aftercare health behavior into their everyday life and (B) people who have stopped the aftercare health behavior. In each group, a minimum of eight people will be interviewed to gather different perspectives on the topic.

#### Aftercare health behavior—Study Part 2

2.2.2

Participants can choose a health promoting behavior with the main focus on physical activity. This may be an offered aftercare program such as IRENA (Intensified Rehabilitation Aftercare) provided by certified rehabilitation centers or another aftercare health behavior with the goal of stabilizing the effects gained during the rehabilitation program. There is no intervention provided by the research team or the rehabilitation center where the participants completed their rehabilitation program.

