A power analysis was conducted with a small effect size as the evidence regarding the efficacy of rehabilitation programs is insufficient. A meta-analysis about the effects of cardio-vascular rehabilitation on health-related quality of life yielded effect sizes of 0.17–0.25 (21). Due to a large heterogeneity in this meta-analysis and because cardio-vascular rehabilitation programs are different from orthopedic rehabilitation programs, a standard mean effect size of 0.10 was chosen. The power analysis with Cohens *f* = 0.05, *α *= 0.05, 1-*β* = 0.80, a correlation among repeated measures of *r* = 0.50 and a design with eight measurement occasions since the start of rehabilitation program using an analysis of variance (ANOVA) with repeated measurements (within-between interaction) resulted in *n* = 360 participants. Considering a dropout after each measurement occasion of 15%, the recruitment of *n* = 1,101 participants is planned.

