#### Data analysis

2.2.4

In order to quantify the effects of psychological determinants on aftercare health behaviors, multilevel models will be calculated. The advantage of multilevel models in the analysis of repeated measures data is their flexibility in dealing with unbalanced data structures, nested samples (e.g., clustering in rehabilitation centers), and missing values (50). This modeling technique is particularly suited for analyzing data that is hierarchically structured, nested in treatment centers or involves repeated measures, thus allowing for the assessment of both individual and group-level variations (e.g., analysis of the influence of programs in different rehabilitation centers). In addition, latent growth curve models will be used to examine the relationships between the growth parameters of intentions, anticipated affect, experienced affect, habit, and aftercare health behaviors. This modeling approach facilitates an in-depth exploration of individual growth trajectories and their interrelations over time, offering valuable insights into the developmental aspects of health behaviors post-rehabilitation.

The interviews will be analyzed using reflexive thematic analysis. Specifically, the six-phase model (51) will be applied. In order to increase the trustworthiness of the analysis, the interviews will be analyzed independently by two persons. In addition, other researchers will serve as critical friends to contemplate alternative interpretations of the interviews (52). These researchers will provide independent perspectives and assist in exploring alternative interpretations, thereby enhancing the depth and credibility of our qualitative findings.

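### The Part 2 target of 226 is 72 × 1.10^12; a 10% weekly loss over 12 weeks calls for 255, and 226 leaves about 64 completers (about 71 if only 11 losses count)

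*Protocol article*

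**What the plan says.** Section 2.2.1 of the protocol article (Sampling and participants, Study Part 2) sizes the quantitative component in G*Power with Cohen's f = 0.10, α = 0.05, power 0.80, "a correlation between the repeated measures of *r* = 0.50" and 12 repeated measures. The test is the within-between interaction of a repeated measures ANOVA. The number of groups is not given. This "resulted in a total sample size of 72 participants". The next sentence adds dropout: "Assuming that 10% of participants drop out of the study each week over a 12-week study period (36), 226 subjects need to be recruited".

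The article explains that the ANOVA stands in for a multilevel power analysis, because the population parameters for the latter were not found in the literature. For the analysis itself, section 2.2.4 says that "multilevel models will be calculated".

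For Study Part 1, section 2.1.1 derives 360 participants for "a design with eight measurement occasions since the start of rehabilitation program", assumes 15% dropout after each occasion, and plans to recruit 1,101.

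**The concern.** A recruitment target that allows for attrition should return the required number once the assumed losses are applied. Here it does not. Increasing a number by 10% does not undo a 10% loss, because 1.10 × 0.90 = 0.99. Over 12 weeks that gap compounds to 0.99^12 = 0.886, so about 11% of the intended completers are missing. The article justifies 226 by the need to retain 72, so the stated 80% power rests on a number of completers that the target does not deliver under the article's own dropout assumption.

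**Working it through.** **Inputs** (protocol article, section 2.2.1, Part 2): f = 0.10; α = 0.05; power 0.80; ρ = 0.50; m = 12 measures; base sample 72; dropout 10% per week over 12 weeks; target 226. From section 2.1.1, Part 1: base sample 360; 15% dropout after each occasion; eight occasions; target 1,101. The number of groups g is not stated, so g = 2 is an assumption, tested in step 1.

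**Step 1: reproduce 72.** For the within-between interaction, λ = f²·N·m / (1 − ρ), df1 = (g − 1)(m − 1), df2 = (N − g)(m − 1), with a noncentral F distribution.
- g = 2, N = 71: λ = 0.01 × 71 × 12 / 0.5 = 17.04, df = 11 and 759, power 0.8006.
- g = 2, N = 72 (rounded up for equal groups): λ = 17.28, df = 11 and 770, power 0.8075. This matches the stated 72.
- g = 3 needs 93 and g = 4 needs 109, so neither gives 72.
- g = 2 also reproduces the 360 of Part 1 (f = 0.05, m = 8, ρ = 0.50).

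**Step 2: reproduce 226.**
- 72 × 1.10^12 = 72 × 3.1384 = 225.97, which rounds to 226.
- 72 / 0.90^12 = 72 / 0.28243 = 254.9, so 255.
- 72 / 0.90^11 = 72 / 0.31381 = 229.4, so 230.
- Dividing by 0.90 week by week, with rounding down, to nearest or up at each step, gives 242, 257 or 260 for 12 losses and 218, 231 or 234 for 11. None is 226.

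**Step 3: check the pattern in Part 1.**
- 360 × 1.15^8 = 1,101.2, the stated 1,101.
- 360 / 0.85^8 = 1,321.1, so 1,322.

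Both targets match the multiplying formula to the integer, at different rates and with different numbers of occasions.

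**Step 4: what 226 leaves, and the power on the planning ANOVA (g = 2).**

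| Losses counted | Recruits needed for 72 | Completers from 226 | Planning power |
|---|---|---|---|
| 12 | 255 | 226 × 0.90^12 = 63.8, about 64 | 0.7465 (λ = 15.36, df = 11 and 682) |
| 11 | 230 | 226 × 0.90^11 = 70.9, about 71 | 0.8006 |

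The shortfall in recruits is 255 − 226 = 29 with 12 losses and 230 − 226 = 4 with 11.

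**The case against.** The strongest reply concerns the count of losses. With 12 measures over 12 weeks, a participant lost after the last measure costs no data. If the first measure is taken at entry, only 11 intervals matter. On that reading 226 is four short of 230 and planning power is still about 80%. This stands as a real alternative and has to be reported. It does not explain where 226 came from, since the exact match is to an exponent of 12, and the text describes loss in each week of a 12-week period.

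A second reply also stands. The 75% is a completers-only figure, and a reader might infer that Part 2 itself will have 75% power. The documents do not support that. Section 2.2.4 plans multilevel models and names their handling of unbalanced data and missing values as an advantage, so dropouts contribute the weeks they completed. With 226 recruits and a 10% loss after each measure, expected person-weeks are 226 × (1 − 0.90^12) / 0.10 ≈ 1,622; with the loss before each measure, about 1,460. The 72 completers would supply 72 × 12 = 864. These counts are not a power calculation, but they show that the actual loss of power may be smaller than the planning figure suggests.

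A reader might also be tempted to go further and fault the description of the planning test, where "the more conservative repeated measures ANOVA is used", or to say that Part 2 has no groups at all. Neither is established. No calculation shows that the ANOVA fails to be conservative, and the article openly presents it as a stand-in. Section 2.2.4 mentions group-level variation between rehabilitation centers, and section 2.2.1 distinguishes people who keep up the behavior from those who stop, though for the interviews. These points are not part of the required correction.

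**Conclusion.** The point holds as an arithmetic error. The target of 226 comes from the wrong inflation formula, the same one used for Part 1, and does not follow from the stated dropout assumption. Under the 12 weekly losses that the text describes, the plan is 29 recruits short, expects about 64 completers instead of 72, and has planning power of about 75% instead of 80%. Under 11 losses the target is four recruits short and planning power is essentially as stated.

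The power figures rest on two assumptions: two groups, inferred because that setting reproduces 72, and an analysis of completers with the planning ANOVA. The origin of 226 and the completer counts depend on neither. The shortfall is moderate and does not call the Part 2 design into question.

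**What to change.** In section 2.2.1 (Part 2), write the inflation as 72 / (1 − 0.10)^k and state k, the number of weekly losses counted. Keep 226 as the target and restate what it delivers: about 64 completers and planning power of about 75% for 12 losses, or about 71 completers and about 80% if 11 are meant. Give the number of groups used in the calculation. Add one sentence saying that these are completers-only ANOVA figures and that the planned multilevel models will also use partial data from dropouts.

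The cost is a few corrected sentences and a slightly less favorable stated power, with no change to design, recruitment or analysis. The correction is best made before Part 2 recruitment begins. The article is not clear on that timing: section 2.2.1 says that Part 2 data collection has not started, while section 2.2.3 gives a start in February 2023. That conflict should be reconciled separately.
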